## Abstract

**Background:**

Lifestyle and diet are important determinants of type 2 diabetes (T2D). Their impact on T2D can be evaluated using clinical and epidemiological approaches. Randomised controlled trials are the most rigorous design but expensive to conduct, whereas prospective cohort studies are time-consuming and less powerful for populations with a low incidence of the disease. Case–control studies are considered appropriate in resource-limited settings. A hospital-based case–control study protocol has been developed to investigate the role of lifestyle and dietary factors in T2D aetiology for adults in Vietnam.

**Methods:**

A total of 1100 patients aged 40–65 years (550 T2D cases and 550 controls) will be recruited from a tertiary hospital in Hanoi, the capital city of Vietnam. Cases and controls will be frequency-matched on age (±3 years), gender, and residential location. T2D will be diagnosed according to the 2006 World Health Organisation criteria. Habitual physical activity will be assessed by the Vietnamese version of the International Physical Activity Questionnaire-Short Form. Food and beverage consumption will be ascertained using a Validated Food Frequency Questionnaire, specifically developed for the Vietnamese population. Information on demographic and other personal characteristics will be collected, together with anthropometric and blood pressure measurements. Descriptive statistics and unconditional logistic regression analyses will be performed to examine factors associated with the T2D prevalence.

**Discussion:**

The proposed study will elucidate the role of lifestyle and diet in T2D prevalence among Vietnamese adults. Findings concerning pertinent factors will provide epidemiological evidence for the development of focused interventions, and contribute to the formulation of national policies to prevent and control T2D in Vietnam.

## Background

The prevalence of chronic non-communicable diseases is rising worldwide, with notable increases being observed in low- and middle-income countries (World Health Organisation 2011). As a major non-communicable disease, type 2 diabetes (T2D) poses public health and socioeconomic challenges. In 2013, the estimated number of people with diabetes was 382 million worldwide, of whom 179 million (~47 %) lived in low- and middle-income countries in Asia (Guariguata et al. 2014). Diabetes caused at least USD 548 billion dollars (11 % of the total health spending on adults worldwide) in 2013 (International Diabetes Federation 2013). The aging population and rapid nutritional transition in many Asian countries appear to be the drivers of the growing prevalence of T2D in this region (Council on Foreign Relations 2014). Therefore, it is important to understand the role of lifestyle and diet in the aetiology of T2D in Asia’s emerging economies.

Vietnam is a lower-middle income country in Southeast Asia with a rapidly growing economy. An early study reported that the prevalence of T2D amongst Vietnamese adults was only 1.2 % in 1994 (Quoc et al. 1994). However, a recent systematic review showed that the prevalence of T2D has doubled from 2.7 % in 2002 to 5.4 % in 2012 (Nguyen et al. 2015). This review also found a lack of epidemiological studies addressing the relationship between lifestyle, diet and T2D in Vietnamese adults. For example, a case–control study (Le et al. 2005) suggested that the elevated risk of T2D was associated with the intake of animal protein and meat, but inversely associated with the consumption of carbohydrate and rice, yet the sample size of the study was rather limited (n = 144), and there was lack of consideration of potential confounders and nutrient inter-correlation in this study.

Modifiable lifestyle and dietary factors provide an opportunity for the management, control and prevention of T2D by implementing effective interventions. Despite accumulating epidemiologic evidence of the association between tea and coffee consumption and the risk of T2D (Ding et al. 2014; Yang et al. 2014), few studies have addressed the role of green tea, a popular beverage in Asia, in T2D aetiology (Iso et al. 2006; Odegaard et al. 2008). Similarly, no study has been conducted concerning the effects of coffee consumption in Vietnam, one of the world’s biggest producers of coffee beans. Tea and coffee are the major sources of catechins (Higdon and Frei 2003) and chlorogenic acids (Higdon and Frei 2006), respectively, the so-called phenolic compounds known for their antidiabetic properties (Kim et al. 2016). Because these compounds vary in amount according to tea processing (Shitandi et al. 2012) and coffee variety (Arabica vs. Robusta) (Pham and Preedy 2015), specific types of tea and coffee can produce different effects on the development of T2D.

Given the widespread consumption of green tea and coffee in Vietnam, it is timely to investigate their relation with the T2D risk, along with the effects of lifestyle and other dietary factors. Case–control, cohort studies, and randomised controlled trials (RCTs) provide an ascending hierarchy of levels of evidence (Colditz 2010). RCTs are the most rigorous design but expensive to conduct, whereas prospective cohort studies require a long-term follow up and less powerful for the population with a low incidence of the disease. Case–control studies, being retrospective in nature with a relatively smaller number of participants, are suitable in resource-limited settings (Wang and Attia 2010). In particular, hospital-based case–control studies, with supporting clinical and laboratory services, are less costly and preferable than their community-based counterparts (Schlesselman and Schneiderman 1982). Therefore, a hospital-based case–control study protocol has been developed to ascertain the role of lifestyle and diet in relation to the T2D risk for adults in Vietnam.

Specific objectives of our case–control study are:To determine the association between green tea consumption and risk of T2D.To determine the association between coffee consumption and risk of T2D.To ascertain common foods in the Vietnamese diet (e.g. soy foods, fruits, vegetables, red/processed meat, and white rice-based products) in relation to the T2D risk.To investigate certain macronutrients (e.g. protein, carbohydrate, and fat) and micronutrients (e.g. magnesium, iron, vitamin D, and minerals) in relation to the T2D risk.To determine the association between lifestyle factors (such as smoking, alcohol drinking, and physical activity) and risk of T2D.

## Methods

The study protocol was designed and presented in accordance with the Strengthening the Reporting of Observational Studies in Epidemiology guidelines (Von Elm et al. 2007).

### Study design

This hospital-based case–control study will recruit T2D cases frequency matched to controls by age and sex on a 1:1 ratio in a hospital in northern Vietnam. Data will be obtained by interviewing patients with and without T2D. Medical records and log-books of eligible cases and controls will be searched for the most recent laboratory test results and medical history information.

### Study setting

The proposed study will be undertaken in a tertiary public hospital located in the catchment covering both rural and urban areas of Hanoi City, the capital of Vietnam. This is a general hospital comprising 600 beds, 39 departments/units, and 853 employees. In 2009, there were 317,343 individuals seeking medical care in this hospital. Currently, about 5000 diabetic patients are being monitored and managed in the outpatient department. On average, 30–40 cases of T2D are newly diagnosed every month, allowing the completion of recruitment within 18 months for the target sample size.

### Sample size calculation

A primary objective is to determine the association between the consumption of green tea, a popular beverage in Vietnam, and the risk of T2D. The green tea exposure is thus used to estimate the required sample size. The available data indicated that 70 % of Vietnamese adults consume 1–6 cups of green tea per week (1 cup ~200 mL). We further postulate that the odds ratio (OR) for T2D is 0.66 among individuals drinking 1–6 cups of green tea per week relative to non-drinkers (Iso et al. 2006). With frequency matching by age and sex between cases and controls on a 1:1 ratio, a total of 1080 subjects (540 T2D cases and 540 controls) will be required to attain 90 % statistical power for such effect size at 5 % level of significance (Schlesselman 1974). To compensate for potential refusal and withdrawal, 1100 subjects (550 cases and 550 controls) will be recruited. The proposed sample size should be sufficient to detect moderate effect sizes for other dietary and lifestyle factors such as coffee consumption and physical activity levels.

### Selection of cases

Potential participants will be identified by searching the medical records of the Department of Endocrinology. The hospital uses the 2006 World Health Organisation (WHO) diagnostic criteria for T2D (WHO 2006) according to the levels of fasting plasma glucose and/or 2 h-oral glucose tolerance test (2 h-OGTT). Consecutive patients newly diagnosed with T2D will be assessed for eligibility when they come to the hospital for treatment. An appointment will be arranged for a personal interview if the patient meet the following selection criteria, agree to participate and can voluntarily provide informed consent.

#### Inclusion criteria

Aged 40–65 years;Diagnosed with T2D within 4 weeks before the interview; andBeing able to undertake a 45-min face-to-face interview including measurements.

#### Exclusion criteria

Deemed too ill to participate by the medical doctors;Diagnosed with T2D more than 4 weeks before the interview;In long-term modification of diet due to any reason; andNon-residents, tourists or foreigners.

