### Selection of controls

Controls will be individuals seeking medical care at the outpatient clinics of the departments of orthopaedics, dental, ear, nose and throat, and gastroenterology, who are generally healthy and unlikely to share similar risk profiles as the cases. As a partner of the national diabetes prevention program, all patients attending the hospital outpatient clinics will be screened and tested for T2D by administering fasting glucose test and/or 2 h-OGTT, results of which are entered into the patient log-book and medical record on the day of their visit. The physician will then confirm their diabetes-free status on the basis of the 2006 WHO diagnostic criteria. Eligible controls, being frequency-matched to cases on sex, age (±3 years), and residential location, will be recruited at the same data collection period as the cases. They will be interviewed by the research assistant using the same questionnaire upon their consent to participate in the study.

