#### Inclusion criteria

Individuals who attend the hospital outpatient clinics due to minor health problems;Whose plasma glucose levels are within the normal range based on the 2006 WHO diagnostic criteria;At the same age group as cases (±3 years); andReside in the same catchment area (metropolitan Hanoi) as the cases.

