#### Dietary assessment

Dietary habits over the three preceding years will be ascertained using a validated semi-quantitative Food Frequency Questionnaire (FFQ), specifically developed for the Vietnamese population (Tran et al. 2013a). This FFQ records the intake of commonly consumed food and beverage items in Vietnam, which are classified into 15 major food groups (soybean products, tomato products, vegetables, fresh fruits, cereal, meat, seafood, egg, cooking oil, seasoning, milk, alcohol, tea, coffee, and juice). The frequency of consumption is documented according to month, week, or day. A portion size (small, standard or large) is estimated via a picture book taken from a previous study (Kusama et al. 2005). Dietary intakes of the 128 food and beverage items, energy and selected nutrients will be computed, with reference to the standard tables of food composition in Vietnam (Khan 2007).

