#### Physical activity assessment

Physical activity levels including vigorous and moderate activities as well as walking before the onset of T2D will be assessed by the Vietnamese version of the International Physical Activity Questionnaire-Short Form (Tran et al. 2013b). Sitting time will be inquired about the amount of time spent using computers, watching television, eating meals, reading newspapers/book and sitting on motorbikes, in vehicle or train. Information about sleeping duration will also be solicited.

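### The diet exclusion is not tied to the three-year FFQ window, so people who changed diet, tea or coffee because of illness before diagnosis enter the models unidentified

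*Protocol article*

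**What the plan says.** The exclusion criteria under Selection of cases and under Selection of controls carry the same line: "In long-term modification of diet due to any reason". Neither list says how long long-term is, or how it relates to the period the questionnaire covers.

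Dietary assessment sets that period: "Dietary habits over the three preceding years will be ascertained using a validated semi-quantitative Food Frequency Questionnaire". It does not say that the three years end before diagnosis or before symptoms. Physical activity assessment does set such an anchor, for vigorous and moderate activity "as well as walking before the onset of T2D will be assessed".

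Two other rules bear on the point. Cases must be "Diagnosed with T2D within 4 weeks before the interview". Controls are "Individuals who attend the hospital outpatient clinics due to minor health problems", drawn from the "departments of orthopaedics, dental, ear, nose and throat, and gastroenterology, who are generally healthy".

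The Statistical analysis section describes adjusted logistic models, interaction tests and trend tests. It describes no analysis that separates people whose diet changed recently. The Discussion covers recall bias and selection bias, but not changes in diet caused by developing disease.

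**The concern.** The green tea, coffee, food and nutrient objectives all need exposure that precedes disease. Type 2 diabetes often has a lead-in before diagnosis in which weight, blood pressure, a borderline glucose or symptoms may prompt a person to change what they eat and drink. If such a person reports the new habit as the three-year habit, the model reads a consequence of early disease as a possible cause of it.

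The diet exclusion looks like the safeguard against this, but it addresses long-term modification only. A change made a few months before diagnosis is not plainly long-term, so the person is enrolled and nothing in the stated data collection marks them. Controls from gastroenterology clinics may also have changed diet recently, for a different reason, so the effect need not cancel between the groups. At stake is whether the reported ORs can be read as exposure before disease.

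**Working it through.** **The plan's own figure.** Sample size calculation gives 70% exposed, OR 0.66, 90% power, 5% level, a 1:1 ratio and 540 per group.
- Exposure in cases: p1 = 0.66 × 0.70 / (0.30 + 0.66 × 0.70) = 0.462 / 0.762 = 0.6063.
- Two-sided comparison of 0.70 with 0.6063, no continuity correction: n = [1.960·√(2·p̄·q̄) + 1.282·√(p0·q0 + p1·q1)]² / (p0 − p1)², with p̄ = 0.6531. This gives 541 per group against the stated 540.
- Power is 0.900 at 540 and 0.905 at 550 per group. The planning figure reproduces and is not in question.

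**What the four-week limit covers.** Three years is about 156.5 weeks. The share of the window taken up by a change of a given age is:

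| Age of change | Share of window |
|---|---|
| 4 weeks | 4 / 156.5 = 2.6% |
| 26 weeks | 17% |
| 52 weeks | 33% |
| 104 weeks | 66% |

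Change after diagnosis is therefore held to 2.6% of the window. Halving intake over those 4 weeks moves a correctly recalled three-year average by 0.5 × 2.6% = 1.3%. Halving it over the last 52 weeks moves the average by 0.5 × 33% = 17%, and no stated rule limits a change of that age made before diagnosis.

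**Effect on the OR (assumed rates; the document gives none).** Suppose the change happens in cases only and the new habit is reported as the three-year habit. Control odds are 0.70 / 0.30 = 2.333.

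Case non-drinkers take up green tea, true OR 0.66:
- 5%: 0.6063 + 0.05 × 0.3937 = 0.6260. OR = (0.6260 / 0.3740) / 2.333 = 0.72.
- 10%: 0.6063 + 0.10 × 0.3937 = 0.6457. OR = (0.6457 / 0.3543) / 2.333 = 0.78.

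Case drinkers stop, true OR 0.66:
- 5%: 0.6063 × 0.95 = 0.5760. OR = (0.5760 / 0.4240) / 2.333 = 0.58.
- 10%: 0.6063 × 0.90 = 0.5457. OR = (0.5457 / 0.4543) / 2.333 = 0.51.

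Case drinkers stop, true OR 1 (70% exposed in both groups):
- 5%: 0.70 × 0.95 = 0.665. OR = (0.665 / 0.335) / 2.333 = 0.85.
- 10%: 0.70 × 0.90 = 0.63. OR = (0.63 / 0.37) / 2.333 = 0.73.

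If controls are the ones who stop, still with a true OR of 1, the last two become 1.18 and 1.37. The same mechanism can hide a true association or create a false one.

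**The case against.** A reader might infer that the exclusion works backwards, removing people with stable, well-measured diets and keeping those whose diets are unstable. The document does not support that.
- Long-term has no stated duration. A diet modified for more than three years would be constant across the window, but one begun one to two years ago may also count as long-term. That change splits the window (33% to 66%), so removing it helps a three-year average.
- A long-standing diet may have been adopted for raised risk or another chronic condition. Excluding it guards against confounding by indication and reverse causation.
- Trimming unusual diets in the same way in both groups costs exposure contrast but does not of itself bias the OR. The size of that loss depends on a prevalence that the document does not give.

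A reader might also infer that green tea's OR is pulled toward 1. That holds only if cases take up tea; if they stop, the OR moves the other way.

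The mitigations have some force. Cases are newly diagnosed, controls have minor problems, interviews are uniform, and the questionnaire asks for three years, not for current habits. The bias above needs people to report current habits in place of the period asked about. But the four-week limit does not reach change before diagnosis, and uniform interviewing does not identify who changed.

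Lastly, this is a condensed article, and a definition of long-term or a diet-change item may sit in the full protocol or the questionnaire. That is fair, and the missing definition alone would be a small matter. What stands is what the article does fix: a window for diet with no anchor before onset, beside an anchor for physical activity, and an exclusion that does not address recent change.

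**Conclusion.** The point holds as a gap in what the exclusion covers, not as an inverted criterion. As written, people who changed diet, tea or coffee before diagnosis or the recruiting visit because of symptoms, illness or medical advice are pooled with everyone else, and the stated analyses cannot separate them.

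The direction of the resulting bias is uncertain. Its size rests on assumed rates and on new habits being reported as the three-year habit. With 5% to 10% of case non-drinkers taking up green tea, a true 0.66 would be seen as 0.72 to 0.78. With 5% to 10% of case drinkers stopping, it would be seen as 0.58 to 0.51. If respondents average faithfully over three years, the effect is much smaller. No sample-size figure changes.

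It is worth acting on before interviews begin, because a date and reason for change that were not asked cannot be recovered later.

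**What to change.** Keep the exclusion in both lists. Then make three changes.
1. Dietary assessment: anchor the FFQ reference period to the three years before diagnosis for cases and before the recruiting visit for controls, in line with the approach already taken for physical activity.
2. Data collection: add one question, put identically to both groups, on the date and reason of any change in diet, tea or coffee within that window. If the questionnaire already holds such an item, say so.
3. Statistical analysis: repeat the diet, tea and coffee models without participants who changed because of illness, symptoms or medical advice, and report both sets of ORs.

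The anchor alone is not enough, since it removes only change after diagnosis; the question and the repeat analysis deal with change before it.

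The cost is one question and one sensitivity analysis on a slightly smaller sample. Losing 10 per group, from 550 to 540, takes power for the planned effect from 0.905 to 0.900. The reason for change is self-reported, so the analysis is a check on the main result and does not replace it.

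Narrowing the exclusion to illness-driven changes within the three years is not advised. It would admit people on medical diets begun more than three years ago, whom the present wording keeps out.

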### Selection of controls

Controls will be individuals seeking medical care at the outpatient clinics of the departments of orthopaedics, dental, ear, nose and throat, and gastroenterology, who are generally healthy and unlikely to share similar risk profiles as the cases. As a partner of the national diabetes prevention program, all patients attending the hospital outpatient clinics will be screened and tested for T2D by administering fasting glucose test and/or 2 h-OGTT, results of which are entered into the patient log-book and medical record on the day of their visit. The physician will then confirm their diabetes-free status on the basis of the 2006 WHO diagnostic criteria. Eligible controls, being frequency-matched to cases on sex, age (±3 years), and residential location, will be recruited at the same data collection period as the cases. They will be interviewed by the research assistant using the same questionnaire upon their consent to participate in the study.

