There are several strengths of the proposed study, namely, a relatively large sample size to assess different exposures, use of validated instruments for diet and lifestyle assessment, ascertainment of exposure variables via structured interviews, and uniform measurements of clinical and biochemical parameters across case and control groups. Special efforts will be made to increase response rates and minimise withdrawal of participants. However, some limitations warrant attention. Case–control designs are inherently retrospective in nature, as such they are susceptible to biases. For instance, selection bias may arise if only severely ill patients are recruited and the controls are drawn from a different reference population. For this reason, we will select newly diagnosed (incident) T2D patients, while non-diabetic controls are recruited from the outpatient clinics of the same hospital, who are matched to the cases in terms of residential location but are unlikely to share the same risk profiles. Moreover, the hospital serves the entire catchment covering both rural and urban areas of Hanoi, so that our sample of participants should be representative of the underlying adult population. Another potential drawback is recall bias (Armenian 2009), which may lead to spurious associations between exposures and the outcome of interest (Gordis 2000). In this study, a consistent recruitment and interview process is adopted throughout the data collection period and applied to both case and control groups, particularly the use of interviewer-administered questionnaires, which should reduce recall error and bias between the two groups.

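### Gastroenterology controls and the aim of controls unlike the cases leave the tea, coffee, alcohol and diet odds ratios open to selection bias of unknown size and direction

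*Protocol article*

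**What the plan says.** Under Selection of controls, the protocol article recruits from the outpatient clinics of the "departments of orthopaedics, dental, ear, nose and throat, and gastroenterology" and describes these patients as people "who are generally healthy and unlikely to share similar risk profiles as the cases".

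The Discussion names selection bias as a limitation. Part of its answer is to use controls from the same hospital "who are matched to the cases in terms of residential location but are unlikely to share the same risk profiles". It then adds, on the ground that the hospital serves rural and urban Hanoi, that "our sample of participants should be representative of the underlying adult population".

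The listed control criteria require a minor health problem, normal glucose, an age matching the cases and residence in the catchment. They exclude cancer, severe illness, long-term dietary change and non-residents. None refers to whether the presenting complaint is related to tea, coffee, alcohol or diet.

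Green tea drives the sample size. Coffee, foods, nutrients, smoking, alcohol and physical activity are the other stated exposures.

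**The concern.** There are two separate weaknesses.

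**The stated principle.** In a case–control study, controls estimate how common the exposure is in the population that produced the cases. The risk profile for type 2 diabetes includes the very factors under study: diet, smoking, alcohol and activity. Wanting controls who lack that profile is therefore not a safeguard. If it were acted on, it would select on exposure. It also sits badly with the representativeness claim in the same Discussion paragraph.

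**The gastroenterology clinic.** People with digestive complaints may drink less tea, coffee or alcohol because of symptoms, or may have complaints that are partly due to higher intake. Either way, their intake need not match that of the source population.

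Covariate adjustment does not repair this. Cases come from endocrinology and controls from four other clinics, so clinic is completely separated from case status and cannot enter the model as a confounder. The distortion lies in the controls' exposure itself. It also cannot be undone after recruitment unless each control's clinic and diagnosis are known.

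**Working it through.** **Inputs from the document (Sample size calculation)**
- Exposure: "70 % of Vietnamese adults consume 1–6 cups of green tea per week", taken as the control prevalence, p0 = 0.70. The remaining 30% are treated as unexposed, which reproduces the plan's figure.
- Effect: "the odds ratio (OR) for T2D is 0.66 among individuals drinking 1–6 cups of green tea per week relative to non-drinkers".
- Error rates: "to attain 90 % statistical power for such effect size at 5 % level of significance". Two-sided testing is not stated but reproduces the figure.
- Design: "frequency matching by age and sex between cases and controls on a 1:1 ratio"; 540 per group required, 550 per group recruited.

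**Step 1. Reproduce the plan's figure**

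Case exposure: p1 = p0·OR / (1 + p0·(OR − 1)) = 0.70 × 0.66 / (1 − 0.70 × 0.34) = 0.462 / 0.762 = 0.6063.

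Per group: n = [1.960·√(2·p̄·q̄) + 1.282·√(p0·q0 + p1·q1)]² / (p0 − p1)², with p̄ = 0.6531 and q̄ = 0.3469.

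n = [1.960 × 0.6731 + 1.282 × 0.6699]² / 0.0937² ≈ 540.2, rounded up to 541, against 540 stated. Power is 0.900 at 540 per group and 0.905 at 550. The sample size is sound. However, its 70% describes Vietnamese adults in general, so the calculation holds only if the controls have that exposure distribution.

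**Step 2. Illustrate the sensitivity**

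The document gives neither the gastroenterology share s nor the proportion g of those patients who drink 1–6 cups a week. Both are assumed here.

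- Mixed control prevalence: pm = (1 − s)·0.70 + s·g.
- Observed odds ratio = case odds / mixed control odds. Case odds are 0.6063 / 0.3937 = 1.54 when the true odds ratio is 0.66, and 0.70 / 0.30 = 2.333 when it is 1.00.
- Power uses the two-proportion formula with 550 per group.

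With s = 0.25 (one clinic of four, equal shares assumed):

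| g | pm | Control odds | True 0.66 appears as | Power | True 1.00 appears as |
|---|---|---|---|---|---|
| 0.70 (no distortion) | 0.700 | 2.333 | 0.66 | 0.905 | 1.00 |
| 0.65 | 0.6875 | 2.200 | 0.70 | 0.81 | 1.06 |
| 0.60 | 0.675 | 2.077 | 0.74 | 0.66 | 1.12 |
| 0.50 | 0.650 | 1.857 | 0.83 | 0.32 | 1.26 |
| 0.80 | 0.725 | 2.636 | 0.58 | 0.99 | 0.89 |

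The high power in the last row is not a benefit, because the estimate is exaggerated.

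Varying the share for a true odds ratio of 0.66:
- s = 0.10: it appears as 0.68, 0.69, 0.72 or 0.63 for g = 0.65, 0.60, 0.50 or 0.80.
- s = 0.40: it appears as 0.72, 0.79, 0.94 or 0.54 for the same values of g.

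The range runs from almost no effect of control choice to one that hides or inflates the association. The sign depends on whether intake in these patients is lower or higher than in the source population.

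**The case against.** The strongest defence is that the risk-profile phrase is description and not a rule. The listed criteria do not screen controls on smoking, weight, activity, tea, coffee or diet. The phrase may have been meant to say that the presenting complaints have nothing to do with diabetes risk. A reader might infer from it that controls are picked for low risk-factor levels and that every lifestyle odds ratio is pushed away from 1. The document does not support that inference, and the illustration above moves the green tea odds ratio in either direction. What stands is that the text speaks of the controls' risk profiles, not their complaints, and that the Discussion offers this as an answer to selection bias.

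The conflict with the representativeness claim is only partial, because that claim rests on the hospital's catchment.

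The safeguards are also real:
- Only minor health problems qualify, although many digestive complaints are minor.
- Long-term dietary change is excluded, but a recent reduction, or one limited to beverages, may not count as such.
- The food questionnaire covers three preceding years, which dilutes a recent change but does not prevent it from colouring recall.
- Three other clinics contribute controls, which dilutes distortion from any one of them.

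Together these shrink the problem. None removes it, because no criterion addresses exposure-related diagnoses.

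Finally, the same test applies to orthopaedic, dental and ear, nose and throat diagnoses. It would be inconsistent to question gastroenterology alone, so the fix below applies the test to all clinics.

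**Conclusion.** The point holds as a risk, not as a demonstrated bias. Controls partly drawn from gastroenterology, with no exclusion of exposure-related diagnoses, leave the tea, coffee, alcohol and diet odds ratios open to selection bias that adjustment cannot remove. The risk-profile wording states the wrong principle for choosing controls and should not be presented as a protection.

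A reader might go further and conclude that the odds ratios are biased, in a known direction and by the amounts tabulated. The document does not support this. The gastroenterology share and the tea intake of those patients are assumptions, and the net error cannot be signed. Nor is the sample size at fault: 541 per group against 540 stated.

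This is an inexpensive improvement worth making before recruitment, not a defect that invalidates the design.

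**What to change.** 1. In Selection of controls and in the Discussion, replace the risk-profile wording with a requirement that each control's presenting condition has no known relation to tea, coffee, alcohol, smoking, diet, physical activity or obesity. Apply it to all control clinics.
2. Drop gastroenterology as a control source. If it is kept, record each control's clinic and presenting diagnosis, and report the green tea and coffee odds ratios with and without the gastroenterology controls.

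Cost: a wording change and one fewer control clinic or, if the clinic is kept, a record of clinic and diagnosis for each control and one extra sensitivity table. Recruitment should bear the loss of a clinic: 550 controls over 18 months is about 31 a month, at a hospital where 317,343 people sought care in 2009. The diagnosis rule will make some attenders at the other three clinics ineligible; the document gives no figure for how many.
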